### CPT

After receiving iTBS, cTBS or sham stimulation to the spastic muscle or the antagonist, all participants will undergo a 30-min session of CPT delivered by licensed therapists. Each session will consist of physical modalities, occupational therapy task training, and manual massage/manipulation. The therapy will be provided Monday through Friday throughout the 2-week intervention period.

### Outcome measures

MEPs are compound muscle action potentials recorded from a target muscle after a single-pulse TMS over the primary motor cortex; they provide an objective index of corticospinal excitability and conduction integrity, with excellent test-retest reliability [Intraclass Correlation Coefficient (ICC) = 0.75–0.94, Kendall's tau = 0.81] (17). In this trial, MEPs will be used to quantify corticospinal plasticity before and after the intervention.

Although the pTBS intervention targets the forearm muscles (FCR and ECRL), MEPs were recorded from the abductor pollicis brevis (APB) because it is a standard target muscle in TMS studies, recommended for its consistent and robust MEP responses and well-defined cortical representation in the primary motor cortex (M1) hand area (17). This approach provides a reliable and comparable measure of overall corticospinal excitability.

Briefly, Ag/AgCl surface electrodes will be placed over the abductor pollicis brevis of the paretic limb. A Magstim 200^2^ stimulator with a 70-mm figure-of-eight coil will deliver 0.2-Hz stimuli to the affected-hemisphere M1 hand area while the participant rests. The following metrics will be obtained: (1) resting motor threshold (RMT), defined as the lowest stimulus intensity eliciting ≥ 50 μV MEPs in ≥ 5 of 10 consecutive trials (17); (2) MEP peak-to-peak amplitude (mV) measured at 120%RMT, averaged across 10 artifact-free trials, as a marker of corticospinal excitability; and (3) MEP latency (ms) from stimulus artifact to onset of the first deflection, reflecting central conduction time. All measurements will be performed by the same assessor at baseline, immediately post-intervention, and at the 2-week follow-up to ensure consistency.

The MAS is the gold-standard instrument for quantifying spasticity. For the upper limb it demonstrates good reliability: inter-rater ICC = 0.781 (95% CI 0.679–0.853), κ = 0.625 (95% CI 0.350–0.801); intra-rater ICC = 0.748 (95% CI 0.671–0.809), κ = 0.593 (95% CI 0.467–0.696) (17). Scores range from 0 (normal tone) to 4 (severe spasticity preventing joint movement), with an additional 1+ grade for mild spasticity. In this study, the same blinded assessor will evaluate the spastic FCR at baseline, immediately after the last session, and at the 2-week follow-up: the elbow is flexed 90 °, the forearm is in neutral, and the wrist is passively extended at ≈1 rad/s; a sustained decrease of ≥1 point is considered a clinically meaningful improvement.

The FMA-UE is a specialized scale designed to evaluate upper limb motor function in stroke patients. The estimated range of its clinically important difference is 4.25–7.25 points (22). It consists of 33 items, covering movements of both the proximal and distal parts of the upper limb. The total score ranges from 0 to 66 points, with each item scored from 0 points (inability to complete the action, accompanied by severe abnormal movements) to 2 points (the action is performed in a standardized way and can be completed smoothly).

The ARAT is a standardized scale used to assess the upper limb motor function of patients with neurological impairments. It has high reliability and internal validity, with an intra-class correlation coefficient ranging from 0.992 to 0.998 (23). The scale consists of 19 assessment items, with a total score of 57 points. The score for each item ranges from 0 points (poor upper limb function, unable to complete the action) to 3 points (good upper limb function, the action is standard and completed smoothly).

The Modified Barthel Index is a widely used standardized scale in clinical practice for assessing activities of daily living. It evaluates an individual's basic daily living abilities, covering 10 items such as feeding, bathing, grooming, dressing, bowel and bladder control, toilet use, transfers, ambulation or wheelchair mobility, and stair climbing. It has good reliability and internal validity, with an intraclass correlation coefficient of 0.95 (24, 25). The scale consists of 10 assessment items, with a total score ranging from 0 (completely dependent on others) to 100 (completely independent), effectively reflecting an individual's degree of self-care in daily life.

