### Statistical analysis

For this study, MEP data will be processed and analyzed statistically using the Statistical Package for the Social Sciences (SPSS, version 26.0). For normally distributed continuous data, repeated-measures analysis of variance will be used for intra-group comparisons and independent-samples *t*-test for inter-group comparisons; for non-normal data, Friedman test and Wilcoxon rank-sum test will be adopted; for count data, Pearson χ^2^ test will be employed. The intraclass correlation coefficient (ICC) will be used to assess the inter-rater reliability of MEPs and MAS (17), and Cronbach's α coefficient will be used to test the internal consistency of scales. A *p* value < 0.05 will be considered statistically significant. The measurement of MEPs will follow the guidelines of the International Federation of Clinical Neurophysiology (27), and the FMA-UE will refer to the criteria for clinically important differences (22). To investigate the therapeutic mechanism, we will examine the association between changes in neurophysiological measures and improvements in clinical behavioral outcomes. Specifically, we will calculate the change scores (from baseline to post-intervention) for each participant in MEP amplitude (or cortical silent period) and in the Fugl-Meyer Assessment for Upper Extremity (FMA-UE) scores. We will then use Spearman correlation analysis to determine whether a significant correlation exists between these two change scores. We hypothesize that participants with greater clinical improvement will also exhibit more pronounced beneficial changes in corticospinal excitability.

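### MEP latency as defined is total cortex-to-muscle conduction time, so a change in it cannot by itself be attributed to the central segment

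*Protocol article*

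**What the plan says.** Outcome measures in the protocol article fixes both ends of the measured path. It first explains that "MEPs are compound muscle action potentials recorded from a target muscle after a single-pulse TMS over the primary motor cortex". The stimulator is then to "deliver 0.2-Hz stimuli to the affected-hemisphere M1 hand area while the participant rests", and "Ag/AgCl surface electrodes will be placed over the abductor pollicis brevis of the paretic limb".

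Three metrics follow: resting motor threshold, peak-to-peak amplitude, and "MEP latency (ms) from stimulus artifact to onset of the first deflection, reflecting central conduction time". The section names no root stimulation, F-wave or other peripheral latency to this muscle, and Table 1 lists only MEPs as a single line. The M-wave described under the stimulation protocol is an amplitude. It is recorded during treatment sessions to keep the peripheral stimulation consistent, so it supplies no conduction time to the thumb muscle.

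On use, "MEPs will be used to quantify corticospinal plasticity before and after the intervention", and "All measurements will be performed by the same assessor at baseline, immediately post-intervention, and at the 2-week follow-up to ensure consistency". For analysis, the Statistical analysis section names repeated-measures analysis of variance within groups and "independent-samples *t*-test for inter-group comparisons". It does not say whether the between-group test takes raw values or changes. Change scores are named only for the correlation with FMA-UE, which uses MEP amplitude or cortical silent period.

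**The concern.** The label assigns the whole interval to the central pathway, whereas the definition covers the pathway from cortex to muscle. In many trials this would be a loose phrase. Here it touches the question under study. The Introduction makes neurophysiological mechanisms a primary objective and central-peripheral synergy a secondary one, and the intervention is applied to forearm muscles of the limb in which latency is recorded. If the arms differed in latency, the printed definition would invite a report of altered central conduction, and the measure does not locate the change.

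A second, smaller matter concerns efficiency. If the between-group t-test is run on raw post-treatment latency, stable differences between people, limb length among them, enter the error term. Baseline latency is already collected and could remove most of that variation.

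**Working it through.** The plan gives no figure for latency, so there is nothing to reproduce. The check has three steps.

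**1. What the definition measures.**
- Start of interval: the stimulus over the motor cortex of the affected hemisphere.
- End of interval: onset of the response in the abductor pollicis brevis.
- Hence total latency = central time + peripheral time, where peripheral time = nerve length / velocity + junction delay.
- Central time = total − peripheral. The peripheral term is not among the listed metrics, so central time cannot be formed.
- Within a person: change in total = change in central + change in peripheral. A constant limb length drops out. A central change passes in full into the total, but the two terms on the right cannot be separated.

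**2. Size of the peripheral part (assumed inputs, not from the documents).** Path 0.65–0.85 m, velocity 50–60 m/s, between-person SD of path length 0.04–0.06 m.
- Peripheral nerve time: 0.65/60 = 10.8 ms to 0.85/50 = 17.0 ms.
- Between-person SD of latency from length alone: 0.04/60 = 0.67 ms to 0.06/50 = 1.2 ms.
- Chance imbalance between two arms of 15 (45 completers / 3, from Sample size estimation): standard error of the difference in mean length = SD × √(2/15), about 1.5–2.2 cm, or about 0.24–0.44 ms. Its expectation under randomization is zero.

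**3. Raw values against change from baseline.** A simulation used 20,000 runs, 15 per arm, two-sided alpha 0.05, a purely central 1 ms shift in one arm and unchanged peripheral conduction. Further assumptions were velocity 55 m/s, central SD 1–2 ms, length SD 0.04–0.06 m and measurement SD 0.7 ms.

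| Central SD (ms) | Length SD (m) | Difference in mean change (ms) | Power, raw post values | Power, change |
|---|---|---|---|---|
| 1.0 | 0.04 | −0.999 | 45% | 76% |
| 1.0 | 0.06 | −1.003 | 37% | 77% |
| 1.5 | 0.04 | −1.001 | 31% | 76% |
| 1.5 | 0.06 | −1.000 | 27% | 76% |
| 2.0 | 0.04 | −1.004 | 22% | 77% |
| 2.0 | 0.06 | −1.001 | 20% | 76% |

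The central shift is recovered in full. The loss with raw values comes from all stable between-person variation, not from limb length alone. In the first row the raw variance is 1.0² + (0.04/55 × 1000)² + 0.7² = 1.00 + 0.53 + 0.49 = 2.02, of which length is 0.53/2.02 = 26%.

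The article's own reliability range for MEPs points the same way. With equal variances at the two visits, the variance of a change is 2(1 − ICC) times the raw variance, and with baseline adjustment it is (1 − ICC²) times.
- ICC 0.75: 2 × 0.25 = 0.50, and 1 − 0.5625 = 0.44.
- ICC 0.94: 2 × 0.06 = 0.12, and 1 − 0.8836 = 0.12.

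The article does not say that this range applies to latency in particular, so it is only a guide.

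**The case against.** The strongest reply is that one descriptive clause is imprecise and little follows from it. Four parts of that reply deserve an answer.

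- **Detection is intact.** A reader might infer that the measure cannot show a central change. The documents do not support that: a central change enters total latency in full, as the third step shows. What is lost is attribution.
- **Limb length does not bias the comparison.** A reader might infer that differing arm lengths would create false differences between groups. Allocation is randomized, so length adds variance and not bias, and it cancels in the repeated measurements that the article plans on the same person.
- **Latency carries little weight.** The hypothesis in the Abstract and the correlation in Statistical analysis name MEP amplitude and cortical silent period. Latency is in neither. The article also does not say that stimulation over the forearm muscle bellies alters peripheral conduction to the thumb muscle. That is a possibility the measure cannot exclude, not a demonstrated effect. This part of the reply stands and limits the impact.
- **The choice of raw or change values is commonly left to an analysis plan.** This also stands: the article's silence is not an error. Baseline adjustment is offered as a free improvement on the unadjusted test that the article names. If the t-test is already meant for changes, that part is met.

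None of this repairs the definition. Even if the full protocol lists a peripheral measure, the printed sentence equates the unsubtracted interval with central conduction.

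**Conclusion.** The metric is mislabelled. As defined it is total cortex-to-muscle conduction time, and a change in it cannot by itself be assigned to the central segment. This conclusion rests only on the article's own definitions and needs no physiological assumption.

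The sizes do rest on assumptions. The peripheral part of about 10.8–17.0 ms depends on the assumed path and velocity. The contrast of about 76% power on change with 20–45% on raw values depends also on the assumed 1 ms effect and the assumed SDs. They illustrate direction and order of magnitude and do not predict this trial's results.

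The consequence is confined to how a latency result may be interpreted and how efficiently it is compared between arms. It would go too far to say that the mechanism analysis fails, since the planned correlation does not use latency.

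**What to change.** In Outcome measures, rename the metric total cortex-to-muscle MEP latency, delete the statement that it reflects central conduction time, and add that a latency change will not be attributed to the central segment.

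In Statistical analysis, compare arms on latency with adjustment for the baseline value, or as change from baseline, in place of an unadjusted t-test on raw values. Baseline adjustment is the safer of the two if latency proves less repeatable than assumed here.

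The cost is a few words in the definition and one line in the analysis. The baseline measurement is already scheduled and no procedure is added. The downside is a slightly weaker mechanistic claim. A central claim could be kept only by also measuring a peripheral latency to the same muscle and subtracting it, which would add a procedure.

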### Safety measurements

Safety monitoring: Immediately after each stimulation session, all possible stimulation-related adverse events—including headache, nausea, neck pain, seizure, mood changes, fatigue, tinnitus, dizziness, somnolence, and syncope, as well as local adverse effects such as skin redness, irritation, paresthesia, or muscle soreness at the stimulation site—will be documented on the Adverse Reaction Record Form; this approach is consistent with standard adverse-event surveillance in non-invasive brain stimulation trials (17). Any adverse events potentially linked to CPT will also be captured on the dedicated Adverse Event Case Report Form (26). The intervention will be discontinued if a participant experiences persistent, moderate-to-severe discomfort at the stimulation site or any other adverse event deemed unacceptable by the investigator.

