Building on this framework, we designed an RCT to formally test these mechanisms and establish clinical feasibility. This protocol makes three contributions: (1) a standardized PMT titration method, (2) first RCT testing the W-shaped model through dual-site pTBS, and (3) a rigorous sham-controlled design. Primary objectives are to evaluate pTBS effects on spasticity/function, investigate neurophysiological mechanisms, and establish safety profiles. Secondary objectives include validating central-peripheral synergy, comparing single vs. dual-site stimulation, and generating effect sizes for future trials.

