## Methods

### Study design

The study is a prospective, single-center, randomized, parallel-controlled design. Fifty-four patients will be randomly assigned to one of three groups (Figure 1): (1) active iTBS+sham cTBS; (2) sham iTBS+active cTBS; (3) active iTBS+active cTBS in 1:1:1 ratio. The trial comprises three phases (Table 1): baseline assessment, post-training assessment (i.e., after 10 sessions) and follow-up assessment (i.e., 2 weeks after the completion of all training sessions). Intervention will be conducted five sessions a week, with a total of 10 sessions. All participants will sign an informed consent form. Adverse reactions will be handled in accordance with the preset protocol. The whole study will be performed at the Department of Rehabilitation Medicine of South China Hospital of Shenzhen University (Shenzhen, Guangdong Province, China). The results will be published in peer-reviewed journals and reported at academic conferences. The protocol is registered with Chinese Clinical Trial Registry (Registration No. ChiCTR2500105190). The trial will be conducted in accordance with the Consolidated Standards of Reporting Trials (CONSORT) guidelines, and the study protocol has been approved by the Institutional Review Board of Ethics Committee of South China Hospital of Shenzhen University (grant no. HNL.S2025041).

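### The only stated time for recording stimulation adverse events is right after each session; no between-session look-back and no enquiry at the 2-week follow-up is stated, although safety is a primary objective

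*Protocol article*

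**What the plan says.** **Timing.** The protocol article, Safety measurements, sets when stimulation harms are recorded: "Immediately after each stimulation session, all possible stimulation-related adverse events" are entered on the reaction form. The list covers systemic events (among them headache, fatigue, mood change, somnolence, seizure and syncope) and also "local adverse effects such as skin redness, irritation, paresthesia, or muscle soreness at the stimulation site".

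**Second form.** The same section adds: "Any adverse events potentially linked to CPT will also be captured on the dedicated Adverse Event Case Report Form". No time window is given for that form.

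**Stopping.** "The intervention will be discontinued if a participant experiences persistent, moderate-to-severe discomfort at the stimulation site", or for any further event that the investigator finds unacceptable.

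**Schedule.** Study design states: "Intervention will be conducted five sessions a week, with a total of 10 sessions". Follow-up is "2 weeks after the completion of all training sessions". Table 1 has rows for MEPs, MAS, FMA-UE, ARAT and the Modified Barthel Index, and none for adverse events at any visit.

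**Role of safety.** The last paragraph of the Introduction lists the primary objectives, which include to "investigate neurophysiological mechanisms, and establish safety profiles".

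**Cortical TMS.** Outcome measures schedules single-pulse TMS of the affected hemisphere at baseline, post-intervention and follow-up. Table 1 also ticks MEPs at screening. The Discussion adds a TMS-EEG substudy in the first 30 participants.

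**The concern.** The collection window does not fit the list of events to be collected. Several listed events can begin or continue hours after a short stimulation: muscle soreness, fatigue, headache, mood change, skin irritation. A form completed only at the end of the session records what is present then. It cannot record what starts that evening, and no question about the time since the last session is stated. After session 10 no further recording is stated, although every participant is due back at T2.

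Because safety is a primary objective, the trial will be cited for its adverse-event rates. If delayed events are not asked about, those rates may be too low and the intervention may look better tolerated than it is. A reader of the results could not tell an absent event from one that nobody asked about.

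**Working it through.** The article gives no figure to reproduce. The check is a count of stated recording points against the schedule, followed by a comparison of the passages.

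**1. Recording points during treatment.** Input: 10 sessions, five a week (Study design). One form per session gives 10 stated recording points and 10 − 1 = 9 between-session intervals. With a Monday start, eight of these are overnight and one is a weekend. Stated look-back questions over the 9 intervals: 0.

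**2. After treatment.** Input: T2 is 2 weeks after the last session, that is 14 days. Stated recording points for stimulation events in that time: 0. As a share of the calendar:
- Monday start (assumed): session 10 is day 12, T2 is day 12 + 14 = 26, and 14/26 = 54%.
- Midweek start (assumed): ten consecutive weekdays span two weekends, session 10 is day 14, T2 is day 28, and 14/28 = 50%.

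This is a share of days, most of them well after exposure. It is not an estimate of the share of events missed.

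**3. Is there another stated route?**
- The second form is for events potentially linked to conventional physical therapy (CPT). It has no time limit, but its scope does not extend to delayed stimulation events.
- Study design refers to a preset protocol for how adverse reactions are handled. Handling is a different matter from when they are sought.
- Table 1 shows no adverse-event collection at T1 or T2.

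**4. Cortical TMS visits.** There are three in the text of Outcome measures and four in Table 1. T2, and screening if the Table 1 tick is meant, fall apart from the intervention sessions. T0 and T1 may share a day with the first or last session. If a stimulation session means one of the 10 intervention sessions, T2 at least has no stated recording. If it means any magnetic stimulation, the TMS visits are covered for events present immediately afterwards. The article does not say which is meant.

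**5. Link to the stopping rule.** Each of sessions 1–9 is followed by another recorded contact, so discomfort that lasts across sessions can be noticed. But the next stated recording is made after the next stimulation. Without onset and duration on the form, discomfort carried over from the previous session and discomfort newly caused are not separated. The article does not define how long *persistent* is.

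**The case against.** The strongest reply is that a stated time is not an exclusive time. The article does not say that events reported at other moments are ignored. Staff see participants at every session, record the M-wave at its beginning and end, and deliver 30 minutes of CPT. A condensed article may leave look-back wording and form fields to the full protocol. Table 1 is also schematic: it ticks the intervention at T2, two weeks after treatment has ended, so a missing row proves little by itself.

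Much of this stands, and it limits the point. A reader might infer any of the following, and the documents support none of them:
- *Persistent discomfort cannot be observed.* It can, because sessions recur on weekdays. After session 10 there is no intervention left to stop, so the follow-up gap does not bear on the stopping rule.
- *Persistent discomfort is the only symptom that can stop treatment.* The same sentence also covers any other event that the investigator finds unacceptable.
- *The form is always completed before CPT.* The Abstract describes a session as stimulation followed by CPT, so completion after CPT is an equally possible reading.
- *The TMS visits are certainly uncovered.* Seizure and syncope on the list, and the reference to practice in brain-stimulation trials, fit a form that covers TMS too.

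What does not stand is the appeal to missing detail. The article chooses a collection time and defends it as consistent with standard surveillance. The criticism is of that chosen time, set against the article's own event list and primary objective. Spontaneous reports may reach staff, but they are not a stated method and are a weak basis for a primary safety objective.

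**Conclusion.** The point holds in limited form. The only stated recording time for stimulation events is immediately after each session: 10 points per participant, no look-back over the 9 intervals, and no stated point in the 14 days to T2. Later-starting events on the protocol's own list have no stated collection point, so the safety profile may be undercounted. The amount cannot be calculated from the documents, and the 50–54% of calendar days should not be read as a proportion of events lost.

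The conclusion rests on two assumptions: that some listed events can begin after the form is completed, which the article does not discuss, and that no enquiry beyond the stated one is made. If the full protocol already contains a look-back and a T2 enquiry, the remaining task is to state them here. Coverage of the TMS visits is an ambiguity to be resolved. This is worth correcting before data collection is complete, but it does not threaten the efficacy comparison.

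**What to change.** In Safety measurements, keep the immediate check and add:
- a look-back on the same form, asking about the time since the last session or visit, at the start of sessions 2–10, at T1 and at T2 (the T2 question covering the 14 days);
- a sentence saying that the form is also completed after cortical TMS assessments;
- fields for onset, duration and severity, so that carried-over and new discomfort can be told apart.

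Add an adverse-event row to Table 1. The discontinuation criterion is left to the sponsor; the added fields only make it possible to see from the record how long discomfort lasted.

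Cost: no new visits, and perhaps a minute or two per existing contact (an assumption, not a figure from the article). Reported adverse-event counts will rise because more is asked. The report should state the recording times, so that the rates are not compared directly with trials that recorded events only after each session.

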**Methods:**

This single-center, three-arm, sham-controlled, single-blind randomized controlled trial enrolled 54 stroke survivors (aged 40–80, 3–12 months post-stroke, Modified Ashworth Scale score ≥1). Participants were randomized in a 1:1:1 ratio to receive a 10-session intervention over 2 weeks (5 days/week). Each session consisted of stimulation followed by 30 min of conventional physical therapy. The stimulation protocols were: Group 1: active iTBS over extensor carpi radialis longus + sham cTBS over flexor carpi radialis; Group 2: sham iTBS + active cTBS; Group 3: active iTBS + active cTBS. Stimulation was delivered using a MagTD stimulator at 110%−120% of the peripheral motor threshold (mean 38.4% maximum stimulator output), with 600 pulses per session (50 Hz burst frequency, 5 Hz theta rhythm).

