### Randomization and blinding

Randomization will be performed using a computer-generated random sequence by an independent statistician who is not involved in participant recruitment or outcome assessment.

Group allocation will be concealed in sequentially numbered, opaque, sealed envelopes, which will be opened by the intervention therapist immediately prior to the first treatment session. Both participants and outcome assessors will be blinded to group allocation. The intervention devices for active and sham stimulation will be identical in appearance and generate similar auditory and tactile sensations. For sham stimulation, the coil will be positioned at an angle that prevents effective peripheral stimulation while maintaining the same sound and vibration as active stimulation. Treating therapists delivering the stimulation will not be involved in outcome assessment or statistical analysis to maintain assessor blinding and minimize bias.

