The distinctive sounds and sensations produced by the active stimulation device posed a significant risk to blinding. To counter this, we implemented a comprehensive strategy. We engineered the sham coil to replicate the sensory profile of the active device and added random timing jitter to mask its rhythmic pattern. This technical approach cut the rate of correct group identification in our pilot study from 38 to 17%. Concurrently, we administered deceptive questionnaires about non-existent sensory details, a tactic that reduced participants' confidence in their guesses to chance levels. We will formally assess unblinding at the trial's conclusion and perform sensitivity analyses to gauge its influence on outcomes. For assessors, blinding was secured by physically separating them from the intervention suite, encrypting all group assignments, and employing multiple independent raters.

A single-center study with a modest sample size (*n* = 54) may limit the generalizability of our findings. Rather than dilute inclusion criteria, we embedded a mechanistic substudy in the first 30 participants: simultaneous TMS-EEG and spinal H-reflex recording to build a Bayesian hierarchical model linking individual excitability profiles to response (27). This won't boost statistical power but provides a prior for phase II trials, preventing wasted resources on suboptimal doses.

To further explore the long-term effects, a future 6-month substudy (*n* = 20) is planned. This substudy will not merely extend observation—it will use wearable EMG to continuously track the time constant of long-term trajectory of spasticity. This would reveal whether durability requires periodic booster sessions, directly informing translational decisions (home-based vs. clinic-based devices).

Based on our pilot study (unpublished), we identified a “high neural noise” phenotype, characterized by PMT variability (CV > 15%) in 23% of participants. Rather than treating this as statistical noise, we will use it as a predictive feature: poor responders with high CV will signal the need for EMG-closed-loop titration in future protocols. This is an adaptive design element nested within the trial logic, not a *post-hoc* fix.

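### Entry to both adverse-event forms depends on presumed cause, so some events have no stated route of capture and any by-arm safety summary is open to differences in attribution

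*Protocol article*

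**What the plan says.** Under Safety measurements, the protocol article describes two records:

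- **Adverse Reaction Record Form.** It covers "Immediately after each stimulation session, all possible stimulation-related adverse events", with an open list of systemic and local symptoms that includes fatigue, skin redness and muscle soreness.
- **Adverse Event Case Report Form.** "Any adverse events potentially linked to CPT will also be captured on the dedicated Adverse Event Case Report Form".

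The section names no recorder. Its closing sentence, on discontinuation, refers to other adverse events in general but does not say where they are recorded.

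Other sections bear on this:

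- **Abstract, Methods:** "Each session consisted of stimulation followed by 30 min of conventional physical therapy".
- **CPT:** this applies in every arm ("all participants will undergo a 30-min session of CPT delivered by licensed therapists"), and the content is physical: "Each session will consist of physical modalities, occupational therapy task training, and manual massage/manipulation".
- **Randomization and blinding:** allocation is in sealed envelopes, "which will be opened by the intervention therapist immediately prior to the first treatment session". Participants and outcome assessors are blinded. "Treating therapists delivering the stimulation will not be involved in outcome assessment or statistical analysis".
- **Introduction, last paragraph:** establishing safety profiles is listed among the primary objectives.

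**The concern.** A form that an event enters only after someone has decided its likely cause makes the event count depend on that decision. Here the decision is hard. Soreness, redness or fatigue in the forearm can follow magnetic stimulation, or massage and task training given minutes later.

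Two things are at stake. The first is completeness: an event thought to be due to neither stimulation nor CPT fits neither form. The second is comparability. Groups 1 and 2 each have one sham site and Group 3 has none. Someone who knew which site was sham might be less ready to link a symptom there to stimulation. That would lower the stimulation-related count in Groups 1 and 2 relative to Group 3 without any true difference.

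**Working it through.** The plan gives no adverse-event rate and no safety figure, so there is nothing to reproduce. The check sets the sections side by side and then bounds the size on assumed inputs.

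**Step 1. Trace each kind of event through the stated rule.**

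| Event | Stated route |
|---|---|
| Noted straight after stimulation, possibly due to it | Adverse Reaction Record Form |
| Arises during or after CPT, potentially linked to CPT | Adverse Event Case Report Form |
| Delayed stimulation effect that surfaces during or after CPT | The stimulation form is tied to the moment after stimulation; the other named form is the CPT one |
| Judged to be neither | None stated |
| Arises between sessions, or after the last session and up to T2 | None stated; after the tenth session there is no later session at which to pick it up |

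The schedule in Table 1 lists no adverse-event assessment at T1 or T2 that would fill the last row.

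**Step 2. Who could attribute differently by arm?**

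The intervention therapist opens the envelope and so knows the allocation. Therapists who deliver stimulation are barred from outcome assessment and statistical analysis. Safety recording has its own section, apart from Outcome measures, so whether the bar covers it is not stated. The Discussion says of the assessors that "blinding was secured by physically separating them from the intervention suite", which makes them less likely to be present straight after stimulation, but it does not say who completes the form. The blinding of the CPT therapists is not stated.

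**Step 3. Size.**

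Input from Sample size estimation: 18 per group, 54 in total. One participant is 1/18 = 5.6 percentage points of an arm.

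Let *p* be the true event risk, equal in all arms, and let *a* be the share of events that are attributed to stimulation. Then:

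spurious difference = *p* × (*a*, dual-active arm − *a*, single-active arm)

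All values of *p* and *a* below are assumptions, shown as a range.

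| *p* | 70% vs 90% attributed | 50% vs 90% attributed | Equal shares |
|---|---|---|---|
| 10% | 0.10 × 0.20 = 2 points (0.4 of 18) | 0.10 × 0.40 = 4 points (0.7 of 18) | 0 |
| 30% | 0.30 × 0.20 = 6 points (1.1 of 18) | 0.30 × 0.40 = 12 points (2.2 of 18) | 0 |
| 50% | 0.50 × 0.20 = 10 points (1.8 of 18) | 0.50 × 0.40 = 20 points (3.6 of 18) | 0 |

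The difference depends wholly on attribution differing by arm. If every event is counted whatever its cause, *a* = 100% in each arm and this term is zero by construction.

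**The case against.** A reader might infer more: that staff who know the allocation must be doing the recording, that the between-arm safety comparison is therefore biased, and that unattributed events are lost. The documents do not support this stronger reading.

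- **Recorder.** None is named. That it is the stimulating therapist is plausible but is an inference. Symptoms are reported by participants, who are blinded.
- **Bias.** It needs attribution that differs by arm, which the documents neither state nor exclude. Confusion between stimulation and CPT is by itself common to all arms. Each single-site arm also has an active forearm site, so even an unblinded recorder would have reason to call forearm soreness stimulation-related. The Statistical analysis section names no between-arm adverse-event test.
- **Loss.** The entry thresholds are wide (possible, potentially linked), the symptom list is open, and the word *also* lets one event go on both forms. The discontinuation sentence shows that other events are at least noticed. Study design points to a preset protocol for handling adverse reactions, and a journal article condenses the full document, which may hold a general log.
- **Timing.** If the first form is completed before CPT starts, redness or soreness noted then cannot come from that day's CPT.

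These points stand, and they limit the conclusion. They do not remove it. The article does more than omit detail: it states a capture rule, and that rule is conditional on cause at both entries. Wide thresholds help ambiguous events but not those judged to be neither. The timing separates immediate effects only; delayed effects and carry-over from earlier days remain mixed. A discontinuation clause is not a recording rule.

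**Conclusion.** The point holds in a limited form. The stated rule ties adverse-event capture to presumed cause in a session where two possible causes follow one another, although safety is a primary objective. Events judged to be neither, or arising outside sessions up to T2, have no stated route of capture. Delayed stimulation effects may appear only as CPT-linked. A by-arm summary is open to differential attribution if the recorder knows the allocation, and only the stimulating therapist is shown to know it.

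The size cannot be determined from the documents. One participant is 5.6 points of an arm. The assumed inputs above give 2 to 20 points, and zero if attribution is the same in all arms. Those figures illustrate sensitivity and do not estimate a bias. Severity is minor to moderate, and the change is a cheap improvement.

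**What to change.** In Safety measurements, replace the two cause-based entries with one rule:

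1. Record every adverse event from the first session to T2 on a single form, whatever its presumed cause, with onset time and body site (ECRL, FCR, elsewhere). Name the recorder.
2. Elicit events from the blinded participant with a fixed checklist, so that the treating therapist does not filter the report.
3. Make all-cause events by arm the main safety summary.
4. Judge causality afterwards, from records that do not show the allocation, by a team member who does not know it and does not rate the MAS. Report attributed events as secondary.

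The MAS rater is excluded in item 4 because site-specific events could hint at the allocation.

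**Cost.** One merged form and a change of wording; treatment and the discontinuation sentence are untouched. Background events will enter the counts and add some noise. The article names only participants and outcome assessors as blinded, so the team must identify a suitable person for item 4.
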